## 1) Analysis of demographic and baseline characteristics

- Demographic and baseline characteristics will be summarized using **descriptive statistics**.
- For **continuous variables**, depending on whether the normality assumption is satisfied, the number of observations, mean, and standard deviation, or the median with 25th and 75th percentiles will be presented.
- For **categorical variables**, frequencies and percentages will be presented.
- To compare continuous variables between groups:
  - If the normality assumption is satisfied, an **independent t-test** will be used.
  - If the normality assumption is not satisfied, a **Wilcoxon rank-sum test** will be used.
- To compare categorical variables between groups:
  - A **Chi-square test** will be used, or

- If more than 25% of cells have an expected frequency < 5, **Fisher's exact test** will be used.
- 

## 2) Efficacy analysis

Efficacy analyses will be performed primarily in the **FAS**, with the **PP set** used for supplementary analyses. All statistical tests will be **two-sided** with a **significance level of 5%**, and **two-sided 95% confidence intervals** will be presented.

For each treatment group and each visit, descriptive statistics will be presented. For changes from baseline at each visit, descriptive statistics and 95% confidence intervals will be presented.

---

### a. Analysis of the primary efficacy outcome

- For each measurement time point, changes in the **NRS score for low back pain** from baseline (week 0) to the end of treatment (week 4) and follow-up (week 12) will be summarized for each treatment group using descriptive statistics (number of participants, mean, standard deviation).
  - For within-group tests of the change in NRS for low back pain (from baseline to week 4):
    - If the normality assumption is satisfied, a **paired t-test** will be used.
    - If the normality assumption is not satisfied, a **Wilcoxon signed-rank test** will be used.
  - To evaluate the effect of the treatment group compared with the control group, an **ANCOVA model** will be used, with:
    - the **treatment group** as a fixed effect, and
    - the **baseline NRS score** as a covariate, analyzing the change in NRS from baseline to the end of treatment (week 4).
  - The **least-squares mean (LSM) difference** between the treatment and control groups, the **two-sided 95% confidence interval** for this difference, and the **p-value** will be presented.
- 

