#### (1) Physiotherapy (Interferential Current Therapy, ICT)

- Two pairs of electrodes (four pads) are attached in a crossed pattern centered on the area where pain is most severe, so that the interferential current focuses on the painful region.
- A medium-frequency alternating current of 4,000–4,100 Hz is applied for 15 minutes, and the intensity is adjusted according to the patient's subjective sensation so that pain is not felt.
- Treatment is administered twice per week for 4 weeks, for a total of 8 sessions.
- Devices used:
  - Catholic Kwandong University International St. Mary's Hospital, Department of Korean Medicine: STRATEC STT-570 (STRATEC Co., Ltd., Korea)
  - Wonkwang University Korean Medicine Hospital: EF-160 (OG Giken Co., Japan)

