### 3) Number of participants and rationale

#### (1) First pilot clinical study

- **Total number of participants:** 46 (multicenter recruitment)
  - Catholic Kwandong University International St. Mary's Hospital: 12 participants
  - Wonkwang University Korean Medicine Hospital: 34 participants
- **Planned number of participants and interventions by group**

| Group | Planned number of participants | Planned interventions                                       |
|-------|--------------------------------|-------------------------------------------------------------|
| I     | 23                             | Usual care (ICT + exercise guidance) + Chuna manual therapy |
| II    | 23                             | Usual care (ICT + exercise guidance)                        |

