### 1) Assignment of subject numbers (Randomization)

- For individuals who have provided **written informed consent** to participate in the clinical trial, a **screening number** is assigned in the order of outpatient visits at screening, as follows:
  - Catholic Kwandong University International St. Mary's Hospital: CK-S001, CK-S002, ...
  - Wonkwang University Korean Medicine Hospital: WK-S001, WK-S002, ...
- After the screening tests, participants who meet the selection criteria and do not meet any exclusion criteria are finalized as study subjects.
- After subject selection, **one person among the research personnel** who is not involved in treatment or assessment and **does not pose any risk of influencing the study results or their analysis** is designated as **unblinded**.
- This unblinded person opens, in order, the **opaque allocation envelopes** prepared based on a **block randomization list** generated by an independent statistician, and assigns a **randomization number** to each participant as follows:
  - Catholic Kwandong University International St. Mary's Hospital: CK-R001, CK-R002, ...
  - Wonkwang University Korean Medicine Hospital: WK-R001, WK-R002, ...
- A single participant cannot be assigned **more than one** randomization number, and each randomization number is assigned to **only one** participant.
- For each participant, the combination of the screening number, randomization number, and initials is used as the **subject identification code** to identify the participant until the end of the clinical trial.

- The randomization list allocates participants to the **usual care + Chuna group (Group I)** and the **usual care-only group (Group II)** in a **1:1 ratio**. The randomization table is generated by an independent professional statistician, and the randomization envelopes are also prepared by a third party not involved in the study.

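### The primary ANCOVA has no site term although recruitment and randomization numbering run by hospital; adding one is nearly free and may narrow the confidence interval modestly

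*Protocol*

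**What the plan says.** Section 15, 2) a of the protocol lists the terms of the primary model for week-4 NRS change: treatment group as a fixed effect and baseline NRS "as a covariate, analyzing the change in NRS from baseline to the end of treatment (week 4"). Section 15, 2) b carries the same approach to the secondary outcomes, with nonparametric tests as an alternative.

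Section 6, 3) (1) sets the total at "46 (multicenter recruitment"), split into 12 at one hospital and the rest at the other ("Wonkwang University Korean Medicine Hospital: 34 participants").

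Section 7, 1) has opaque envelopes, prepared from a "block randomization list", opened in order. Randomization numbers form one series per hospital: "CK-R001, CK-R002" and so on, and "WK-R001, WK-R002" and so on. The ratio is 1:1. The list is described in the singular, and stratification by site is not mentioned.

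Section 5.2.1 (1) names a different ICT device for each hospital; the larger one uses the "EF-160 (OG Giken Co., Japan"). Frequency range, duration and the way intensity is set are common to both.

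**The concern.** Separate number series, with envelopes opened in order, make it natural to think that each hospital works through its own blocked sequence. The arms would then be close to balanced within each hospital. An analysis should normally reflect such a restriction. If the hospitals differ in mean NRS change and site is left out, the between-site variation stays in the residual although the design has already removed it from the treatment contrast. The reported standard error is then too large.

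If the list is instead common to both hospitals, chance imbalance of the arms across sites adds variability to the unadjusted estimate, which a site term would remove.

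At stake is some width of the primary confidence interval and some power in a trial of 46. Because the protocol lists the model terms, this is a choice it has made and not a detail left open.

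**Working it through.** **Inputs from the protocol.** Site sizes 12 and 34 (section 6, 3) (1)). Mean NRS change 3.02 (SD 1.72) and 1.36 (SD 1.75), two-sided 5%, 80% power, 20% dropout (section 6, 3) (2)).

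**Assumed, because the documents give no figure.** A between-site difference D in mean change, in within-site SD units, from 0 to 1.0. For the simulation also: a within-site SD of 1.735, and a correlation of 0.3 between baseline NRS and the change.

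**1. The plan's own figure.** Pooled SD = √[(1.72² + 1.75²)/2] = 1.735; d = 1.66/1.735 = 0.957, stated as 0.96. n = 2 × (1.96 + 0.84)²/0.96² = 17.01, rounded up to 18 per group; 18/0.8 = 22.5, rounded up to 23. The stated numbers reproduce. The calculation has no site term, so nothing below changes them.

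**2. Interval width by formula.** With p = 12/46, p(1 − p) = 0.193. Take arms balanced within site and residual variance 1 with site in the model.

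- Without site: residual df = 43 and expected residual variance = 1 + (46/43) × 0.193 × D².
- With site: residual df = 42 and residual variance 1.
- Ratio of 95% CI half-widths (without/with) = (t₄₃/t₄₂) × √[1 + (46/43) × 0.193 × D²], where t₄₃/t₄₂ = 2.0167/2.0181 = 0.9993.

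Example, D = 0.5: 0.9993 × √(1 + 0.0516) = 1.025.

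| D (SD) | In NRS points (× 1.735) | Half-width ratio, without/with site |
|---|---|---|
| 0 | 0 | 0.999 |
| 0.2 | 0.35 | 1.003 |
| 0.3 | 0.52 | 1.009 |
| 0.5 | 0.87 | 1.025 |
| 0.8 | 1.39 | 1.063 |
| 1.0 | 1.74 | 1.098 |

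The break-even, where the lost degree of freedom is repaid, is at about D = 0.08. With N = 36 the ratios are nearly the same (1.025 at 0.5 SD, 1.099 at 1.0 SD).

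**3. Simulation, exact 1:1 balance within site** (6,000 trials per setting; effect 1.66 for all columns except type I error). Each cell is without site / with site.

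| N (sites) | D | Sampling SD of estimate | Mean CI half-width | Type I error | Power |
|---|---|---|---|---|---|
| 46 (12, 34) | 0 | 0.485 / 0.485 | 0.990 / 0.991 | 0.055 / 0.055 | 0.908 / 0.908 |
| 46 (12, 34) | 0.5 | 0.499 / 0.499 | 1.017 / 0.991 | 0.047 / 0.052 | 0.896 / 0.907 |
| 46 (12, 34) | 1.0 | 0.495 / 0.494 | 1.096 / 0.993 | 0.032 / 0.051 | 0.862 / 0.899 |
| 36 (10, 26) | 0.5 | 0.568 / 0.568 | 1.164 / 1.133 | 0.045 / 0.049 | 0.807 / 0.819 |
| 36 (10, 26) | 1.0 | 0.565 / 0.563 | 1.257 / 1.134 | 0.028 / 0.046 | 0.755 / 0.818 |

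The 36 are the 2 × 18 left after the planned dropout; their 10:26 split is assumed. Simulation error on a 5% rejection rate is about √(0.05 × 0.95/6000) = 0.003.

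The sampling SD is the same with or without site. What changes is the reported standard error: at D = 1.0 and N = 46 it is about 1.096/2.017 = 0.543 without site, against a true 0.495.

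**4. Simulation, allocation not stratified** (N = 46). The estimate itself is more variable without site: SD 0.516 v 0.508 at D = 0.5, and 0.542 v 0.498 at D = 1.0. Power is 0.893 v 0.900 and 0.846 v 0.899. The reported standard error without site at D = 1.0 is about 1.092/2.017 = 0.541, in line with the sampling SD of 0.542, so the test is not anti-conservative here either.

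**The case against.** The strongest case against is that the loss is conditional and probably small. Nothing in the protocol says that the hospitals differ in NRS change. Up to 0.3 SD the interval widens by less than 1%. A difference of 1.0 SD, 1.74 NRS points, exceeds the whole planned treatment effect of 1.66. The trial calls itself a pilot with an exploratory aim. All of this stands, and it makes the point minor.

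Three stronger readings are tempting and are not supported:

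- **That the estimate is less precise than the design allows.** Under site-wise blocking its sampling SD is unchanged; only the reported standard error is too large, and only if the sites differ. The estimate itself loses precision only if allocation is not stratified.
- **That the arms are balanced within site by design.** The separate number series suggest it, but the protocol speaks of one list and never states stratification.
- **That unequal site size or different ICT devices reduce precision in themselves.** Both arms at a hospital receive the same ICT. The device matters only if it shifts outcomes between hospitals, and the documents do not say that it does.

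It is also fair to object that a site term cannot simply be added to the nonparametric tests that section 15, 2) b allows. That stands, so the change is limited to the ANCOVA models.

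**Conclusion.** The point holds as a minor one. The primary model leaves out site although recruitment and randomization numbering are by hospital, and a site term helps, or costs almost nothing, under either reading of the allocation. By assumption the primary confidence interval is about 0.3% wider at a between-site difference of 0.2 SD, 2.5% at 0.5 SD and 10% at 1.0 SD; with no difference there is no loss.

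A reader might infer that the trial falls below its 80% power. In the settings tabulated this occurs without site only with 36 participants and a 1.0 SD difference (0.755 v 0.818); at 0.5 SD power stays above 80% either way. There is no bias, no inflation of type I error and no change to the sample size. The figures rest on the 12:34 split and the assumed site differences; those for power and type I error rest also on a within-site SD of 1.735 and a baseline correlation of 0.3.

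**What to change.** In section 15, 2) a, add site as a fixed effect alongside treatment group and baseline NRS. In section 15, 2) b, do the same for the ANCOVA models of the secondary outcomes. Specify this before any unblinded data are seen, since a site term added later would be a post hoc choice. In section 7, 1), state whether the block list is stratified by site.

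The cost is one residual degree of freedom (43 to 42 at N = 46), one model term and one sentence. The sample size stays at 23 per group.

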### b. Analysis of secondary efficacy outcomes

Secondary efficacy outcomes will be analyzed using methods consistent with those for the primary efficacy outcome, focusing on changes from baseline (week 0) to the end of treatment (week 4) and follow-up (week 12).

- ① **Change in NRS for leg pain (radiating pain)**
  - The change in NRS for radiating leg pain from baseline to weeks 4 and 12 will be analyzed.
- ② **Evaluation of subjective pain intensity and quality of life related to low back pain**
  - Changes in the following outcomes from baseline to week 4 and week 12 will be analyzed:
    - ODI,
    - EQ-5D,
    - RMDQ.

For these continuous variables, within-group tests and between-group comparisons will be performed in the same manner as for the primary outcome (paired t-test or Wilcoxon signed-rank test for within-group changes; ANCOVA or appropriate nonparametric tests for between-group comparisons, as appropriate).

---

### c. Exploratory efficacy analysis

Exploratory outcomes will be analyzed as follows:

- **Additional procedures/surgery after the study**
  - ▶ Evaluation of additional nerve block procedures or surgery after the end of treatment
    - Within 8 weeks after the end of the treatment period, it will be investigated whether participants received additional procedures for pain control (e.g., **nerve block procedures**, radiofrequency ablation) or underwent **lumbar surgery**. Based on these data, the **rate of additional procedures** will be evaluated.
    - If significant differences between treatment groups are identified, **post-hoc tests** will be performed.
    - Between-group comparisons of the rates of additional procedures or surgery will be conducted using the **Chi-square test** or **Fisher's exact test**.
    - *Additional procedure rate* =  

$$\left( \frac{\text{Number of patients who underwent additional procedures or surgery}}{\text{Number of patients who completed the study}} \right) \times 100$$
- **Rate of early termination of treatment**
  - ▶ Evaluation of the early termination rate

- Among participants whose treatment was completed early because they met the predefined criteria for **treatment completion prior to the scheduled end of therapy**, the **rate of early termination** will be evaluated for each group.
  - Between-group comparisons of the early termination rate will be conducted using the **Chi-square test** or **Fisher's exact test**.
  - *Early termination rate* =  

$$\left( \frac{\text{Number of patients whose trial participation was terminated early}}{\text{Number of patients who completed the study}} \right) \times 100$$
  - **Analysis of rescue medication use**
    - ▶ Analysis of rescue medication use
      - For each participant, information on the **type of rescue medication used**, **dose**, and **timing of administration** will be collected.
      - For each treatment group, the number of uses and total amount of rescue medication by drug type will be compared between groups using an **independent t-test**, or, if the normality assumption is not satisfied, a **Wilcoxon rank-sum test**.
- 

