## 9. Criteria for discontinuation/withdrawal and early termination of the clinical trial

### ○ Criteria for discontinuation/withdrawal

1. The following medications, which are expected to affect the evaluation of the effectiveness of the interventions, **must not be taken from screening until completion of the clinical trial**.

① Strong opioid analgesics; local anesthetics and corticosteroid preparations administered separately from the trial interventions by the attending physician.

- However, based on the clinical judgement of the investigator, non-steroidal anti-inflammatory drugs and muscle relaxants that are prescribed as needed may be used (see 11. Rescue medication).

② Any other drugs that, in the judgement of the clinical trial investigator, may pose a risk to the participant or introduce bias into the evaluation of the study results.

2. Cases in which the participant requests discontinuation of the trial intervention during the clinical trial, or withdraws consent to participate in the study.
3. Cases in which a serious adverse event occurs and the investigator judges that continuation of the trial is not possible.
4. Cases in which major protocol violations such as violation of inclusion/exclusion criteria are newly identified during the clinical trial.
5. Cases in which, although the early termination criteria are not met, the participant does **not attend at least 5 out of the planned 8 treatment sessions**.
6. Any other cases in which it is considered difficult for the participant to continue in the clinical trial, and the principal investigator/sub-investigator judges that the trial should be discontinued for that participant.

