#### 4. Exploratory efficacy outcomes

- From the end of the 4-week treatment period until the 12-week follow-up, the following are investigated and compared between groups as exploratory outcomes:
  - ① Whether additional **invasive procedures** for low back pain were performed
    - e.g., injection therapy such as **nerve blocks, radiofrequency ablation, or lumbar surgery**.
  - ② Whether **strong opioid analgesics** were used for pain control.
  - ③ **Rate of early termination of treatment** due to sufficient symptom improvement (based on the early-termination criteria).
  - ④ **Use of rescue medications**
    - Type, dose, and frequency of rescue medications (NSAIDs, muscle relaxants, etc.) are recorded and analyzed.

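### The additional-procedure rate divides by study completers, an undefined subset that a counted event may itself reduce, so the result need not be a proportion

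*Protocol*

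**What the plan says.** **The rate.** Section 15, 2) Efficacy analysis, part c, covers this item: "Evaluation of additional nerve block procedures or surgery after the end of treatment". The window is weeks 4 to 12: "Within 8 weeks after the end of the treatment period, it will be investigated whether participants received additional procedures for pain control". Radiofrequency ablation and lumbar surgery are counted too. The numerator is "Number of patients who underwent additional procedures or surgery" and the denominator is "Number of patients who completed the study". Arms are compared by Chi-square or Fisher's exact test.

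**The outcome list.** Section 14.1, item 4, has the same window: "From the end of the 4-week treatment period until the 12-week follow-up, the following are investigated and compared between groups as exploratory outcomes". It introduces nerve blocks with the words "injection therapy such as". Strong opioid use is listed there as a separate outcome. Section 8, 4) (6) collects the same information.

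**The withdrawal criteria.** Section 9, item 1, concerns drugs that "must not be taken from screening until completion of the clinical trial". The first entry is "Strong opioid analgesics; local anesthetics and corticosteroid preparations administered separately from the trial interventions by the attending physician". Section 7, 4) adds that a participant is withdrawn if a concomitant medication is expected to affect the trial's pharmacodynamic or safety evaluation.

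**The analysis set.** Section 15 makes the FAS primary for efficacy: randomised, treated at least once, and with at least one post-baseline efficacy assessment.

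**The concern.** Two features of the formula pull against the rest of the protocol.

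First, the denominator is decided after randomisation and is not defined. Section 9 says that participants who stop early because of improvement are not in the withdrawal group, but no section says whether they, or anyone else short of Visit 11, have completed the study. The trial is open-label and plans for 20% dropout, so completers may differ between arms for reasons tied to treatment.

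Second, the same event can add to the numerator and subtract from the denominator. The Section 9 prohibition runs to the end of the trial and so covers the whole outcome window.

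At stake is the protocol's comparison of later invasive care between arms. The reported rate would be inflated, more so in the arm with more events, and the planned test would have no well-defined table.

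**Working it through.** **Planned size (sets the scale only).** Section 6, 3) gives n = 2 × (1.96 + 0.84)² / 0.96² = 17.01, rounded up to 18 per group. With 20% dropout, 18 / 0.8 = 22.5, rounded up to 23. This reproduces and is not in dispute. The protocol gives no expected procedure rate, so all event counts below are assumptions.

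**Notation, per arm.** N = 23 randomised; x = participants whose procedure also ends participation; w = other withdrawals.

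- As written: x / (N − x − w)
- Per randomised: x / N
- Per participant with the outcome known, if the w others are unknown: x / (N − w)

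| x | w | As written | Per randomised | Per outcome known |
|---|---|---|---|---|
| 1 | 3 | 1/19 = 5.3% | 1/23 = 4.3% | 1/20 = 5.0% |
| 2 | 2 | 2/19 = 10.5% | 2/23 = 8.7% | 2/21 = 9.5% |
| 3 | 3 | 3/17 = 17.6% | 3/23 = 13.0% | 3/20 = 15.0% |
| 5 | 0 | 5/18 = 27.8% | 5/23 = 21.7% | 5/23 = 21.7% |

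**Why no table follows.** Take x = 3, w = 3. The 17 completers are all event-free, and the 3 participants with events are not among them. Events plus non-events make 3 + 17 = 20, but the formula's denominator is 17. Forcing the row to total 17 gives 3 events and 14 non-events, so 3 observed non-events are lost.

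**Effect on a comparison.** Assume 1 event in one arm, 5 in the other, and w = 0.

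- As written: 1/22 = 4.5% against 5/18 = 27.8%, a difference of 23.2 points. With completers forced in as row totals, Fisher's p = 0.073.
- Per randomised: 1/23 = 4.3% against 5/23 = 21.7%, a difference of 17.4 points. Fisher's p = 0.187.

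**Size within planned dropout.** 20% of 23 is 4.6, about 5. If total loss (x + w) is at most 5 per arm, the excess over the rate per randomised is largest at x = 5, w = 0: 27.8% − 21.7% = 6.0 points before rounding. At x = 2, w = 2 it is 10.5% − 8.7% = 1.8 points.

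**Which events are affected.** Section 9 names drugs, not procedures. The link to a nerve block runs through the drug injected. Radiofrequency ablation and lumbar surgery are not listed; such a participant can remain a completer and then sits correctly in both parts of the ratio. The distortion therefore grows with the share of events that end participation.

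**The case against.** The best defence is that several stronger readings fail.

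- **A reader might infer that every counted procedure triggers withdrawal.** Section 9 does not name nerve blocks, ablation or surgery. A block is caught only if it uses a listed drug or the investigator's judgement applies.
- **A reader might infer that treatment failures vanish and the rate falls to about zero.** That needs a numerator restricted to completers, and the formula states no such restriction. Section 8, 5) also provides an assessment 8 weeks after the last session for those who stop early. For someone who finished treatment this is about week 12, so events can usually still be ascertained. Mis-scaling is likelier than loss.
- **A reader might think that the rate counts drugs.** It does not; strong opioid use is a separate outcome. It does meet the Section 9 conflict directly, because strong opioids are named there.
- **A reader might call the omission of weeks 0 to 4 an error.** All three places that define the outcome start at the end of treatment. That is a consistent design choice.
- **A reader might stress that the ratio can exceed 100%.** It can, but only when events outnumber completers, for example 12/11 with w = 0. That means losing more than half of an arm, far beyond the planned 20%.

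The defence can add that the outcome is exploratory and the trial is a 46-person pilot. All of this stands and limits the size of the point. It does not rescue the denominator, which remains undefined, outside the FAS, and open to reduction by the event being counted.

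**Conclusion.** The concern holds in a limited form. The formula divides by an undefined post-randomisation subset and departs from the analysis set that the protocol names for efficacy. If a nerve block uses a local anesthetic or corticosteroid, and its use ends participation as Sections 9 and 7, 4) indicate, the rate is not a proportion and the planned test cannot be laid out from it.

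The direction is upward. With total losses within the planned dropout, the overstatement is up to about 6 percentage points per arm against the rate per randomised. The event counts behind that figure are assumed. Severity is minor: the primary week-4 ANCOVA does not depend on this rate.

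**What to change.** 1. Keep the weeks 4 to 12 window.
2. Replace the completer denominator with one fixed denominator per arm, and name it: either the FAS as Section 15 defines it or all randomised participants. The two sets differ and should not be used interchangeably.
3. Count each participant in that set with at least one listed procedure or surgery, whether or not withdrawal follows. Take the information from Visit 11 or from the early discontinuation visit.
4. Report how many participants in each arm have no information on the outcome, and state how they are counted. Section 15 does not impute non-continuous variables, and in the illustration this choice moves 13.0% to 15.0%.
5. Compare arms by Fisher's exact test on those counts.
6. If completion is used anywhere else, define it.
7. Reconcile Section 7, 4), Section 8, 4) (6), Section 9, Section 14.1 item 4 and Section 15 part c on whether an outcome event, including strong opioid use, also ends participation. Which clinical rule applies is for the sponsor and investigators.

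The cost is one reworded formula and a few clarifying sentences, with no new visit. The reported rates may be slightly lower than under the present formula.

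### Both exploratory rates are divided by an undefined group of study completers, and early termination of treatment is assigned to weeks 4–12, when no treatment is given

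*Protocol*

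**What the plan says.** **Rates.** Protocol Section 15, 2) c prints two formulas.

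- Additional-procedure rate: "Number of patients who underwent additional procedures or surgery" over "Number of patients who completed the study". The period is "Within 8 weeks after the end of the treatment period".
- Early-termination rate: "Number of patients whose trial participation was terminated early" over the same denominator. The event is described as "treatment completion prior to the scheduled end of therapy".

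Both rates are to be compared between groups by a chi-square or Fisher's exact test.

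**Windows.** Section 14.1 item 4 opens its list of exploratory outcomes with one common period: "From the end of the 4-week treatment period until the 12-week follow-up, the following are investigated and compared between groups as exploratory outcomes". The list covers invasive procedures, strong opioid use, "Rate of early termination of treatment" and rescue medication.

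**Related rules.** Section 9 lists strong opioids, and local anaesthetics and corticosteroids given outside the trial interventions, under its discontinuation and withdrawal criteria; these "must not be taken from screening until completion of the clinical trial". The same section keeps participants stopped early for improvement out of the withdrawal group and treats them as fully compliant. Section 15 makes the FAS the main efficacy set.

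**The concern.** The protocol fixes these formulas and windows itself, so they are not details left open for a later document. Three features cause trouble.

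1. The denominator is an undefined subset formed after randomisation. Who stays in it can depend on treatment and on the outcome being counted.
2. Some counted events may remove the participant from that subset. Ending participation early is one. A nerve block with drugs named in Section 9 is another.
3. A single week 4–12 window is applied to outcomes that arise, wholly or partly, in weeks 0–4.

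In an open-label trial with 23 participants per arm, a few people moved in or out of the denominator change the reported percentage noticeably. If the term stays undefined, the choice could be made after the data are seen. Rescue use in weeks 0–4 also matters for interpretation, because the primary comparison is the change in back pain at week 4.

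**Working it through.** The protocol gives no expected value for either rate, so there is no stated figure to reproduce. The event counts below are assumptions.

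**Inputs**

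- Randomised per arm: 23 (Section 6, 3)).
- Withdrawn per arm: 5, the planned 20% dropout (23 − 18 = 5).
- Early terminations for improvement in one arm: assumed 5, then 10.

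**Early-termination rate under three denominators**

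| Denominator | 5 early terminations | 10 early terminations |
|---|---|---|
| All randomised | 5/23 = 21.7% | 10/23 = 43.5% |
| Completers, early terminators included (23 − 5 = 18) | 5/18 = 27.8% | 10/18 = 55.6% |
| Completers, early terminators excluded (18 − 5 = 13; 18 − 10 = 8) | 5/13 = 38.5% | 10/8 = 125% |

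In the last row numerator and denominator do not overlap, so the result is a ratio of two separate groups and not a proportion. Taking the printed denominator as the total for a chi-square or Fisher table would leave 8 − 10 = −2 participants without the event in the second case.

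In the middle row the result is a proper proportion, but of a post-randomisation subset. It equals the all-randomised rate only when nobody withdraws.

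**Additional-procedure rate.** Assume 2 participants have a nerve block with a drug named in Section 9 and are withdrawn for it, within the 5 withdrawals.

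- All randomised: 2/23 = 8.7%.
- Formula as printed: 2/18 = 11.1%, with both cases outside the denominator.

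**Windows, side by side**

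- Early termination: Section 14.1 item 4 says weeks 4–12, while Section 15, 2) c says before therapy was due to end. Treatment runs for 4 weeks (Section 5.2). Read literally, Section 14.1 makes the count zero under any denominator.
- Rescue medication: Section 14.1 item 4 says weeks 4–12, while Section 11 permits it from screening and requires date and dose in the diary.
- Procedures, surgery and strong opioids: Section 14.1 item 4 and Section 8, 4) (6) agree on the period from end of treatment to follow-up. That period suits them.

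**The case against.** A reader might infer that both rates are wrong by construction. The documents do not support that. Sections 9 and 10 treat participants stopped early for improvement as fully compliant, and Section 15 includes completion of treatment because of improvement among its per-protocol conditions. This favours counting them as completers. On that reading the early-termination rate is an ordinary proportion and the planned tests apply; a figure above 100% needs the opposite reading. What stands is that no section says which reading holds, and that even the favourable one conditions on completing.

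A reader might also infer that nerve-block cases vanish, giving a rate of zero. The printed numerator is not limited to completers: with 3 of 23 treated and withdrawn and no other loss, it gives 3/20 = 15%, not 0%. Surgery and radiofrequency ablation are not named as discontinuation criteria, and no strong-opioid rate uses this denominator.

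Nor is early termination unobservable, or early rescue use unrecorded. Section 8, 4) (6) applies the post-treatment window only to procedures, strong opioids and surgery. Section 15, 2) c places early termination correctly and sets no week 4–12 limit on the rescue comparison. The window fault is a conflict between Section 14.1 and the rest of the protocol.

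Finally, Section 8, 5) already plans a visit 8 weeks after the last session for participants who stop early, partly by telephone. That reduces the missing information, but does not settle the denominator.

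**Conclusion.** The point holds in a limited form. The completer denominator is undefined, departs from the FAS and can exclude people counted in the numerator. Under the assumed counts (23 randomised, 5 withdrawn, 5 early terminations) the same data give an early-termination rate from 21.7% to 38.5%. If early terminators are not completers, the formula does not yield a proportion suited to the planned tests. The nerve-block overlap assumes that the block uses a drug named in Section 9 and that the participant is then withdrawn.

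Section 14.1 item 4 contradicts Section 15, 2) c on when early termination is counted, and its window omits rescue use in weeks 0–4.

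The change is worth making because it is cheap. The outcomes are exploratory in a 46-participant pilot, and the primary week-4 ANCOVA is not affected.

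**What to change.** - **Denominator.** In Section 15, 2) c, use all randomised participants per arm, or the FAS, for both rates. If a completer-based rate is kept as a supplement, define completion and say whether early termination for improvement counts.
- **Windows.** In Section 14.1 item 4, count early termination from randomisation to week 4. Report rescue use for weeks 0–4 and weeks 4–12 separately. Keep weeks 4–12 for procedures, surgery and strong opioids.
- **Ascertainment.** Use the visit in Section 8, 5) to ask about these events in participants who leave early. For someone whose last session is in week 2, that visit falls at about week 10 and no later follow-up is planned, so state how the remaining weeks are treated.
- **Reconciliation.** Section 9 must be reconciled with Sections 14.1 and 15, 2) c on events that are both exploratory outcomes and discontinuation criteria. No position is taken here on the clinical rule.

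The cost is a wording change and a few questions at a visit already planned. The one downside is that participants lost to follow-up stay in the denominator with unknown status. Their handling should be stated, for example with a sensitivity analysis, so that they are not silently counted as event-free.
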